## Methods

### Study design, setting, and participants

#### Study design and sampling

This study is a prospective multi-center cohort study sponsored by the Shanghai Children’s Medical Center affiliated to the School of Medicine, Shanghai Jiao Tong University and performed in three cities in southern, central, and northern China, namely, Zhongshan, Guangdong Province, Qufu, Shandong Province, and Dalian, Liaoning Province. According to socioeconomic level and geographical distribution, the districts of Zhongshan, Qufu, and Dalian are stratified into urban districts in the central area and suburban districts in suburban areas. Using a stratified cluster random sampling method, districts and schools will be selected according to geographical location and school size by a random number generator. Grade 1, 2, and 3 children (6 to 10 years old) from primary schools will be included in this study. However, participants with overweight or obesity with a history of hormone treatment in the past 6 months as reported by parents in the questionnaire will be excluded.

We will carry out a nested case-control study, which will be nested in this cohort study. Participants in case-control study will be enrolled in four groups: children with normal weight and normal puberty, with normal weight and precocious puberty, with overweight/obesity and normal puberty, and with overweight/obesity and precocious puberty. And they will be measured body composition, collected venous blood, and stool at baseline, and collected urine samples at baseline and follow-up periods.

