**Children’s health and family environment questionnaire (all participants)**			
Lifestyle	√	√	√
Family environment	√	√	√
Parental information	√	√	√
Early life information	√	√	√

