#### Physical examination

Anthropometric data, including weight (kg), height (cm), and waist circumference (cm), will be measured for each child standing without shoes and lightly clothed using standard techniques by one observer at baseline and the first and second visit. Waist circumference will be measured midway between the lower edge of the rib and the upper edge of the ilium. All of the measurement indexes will be measured twice and averaged. Overweight and obesity are the main predictors of interest and will be defined by BMI value, which is calculated as weight (kg) divided by height squared (m^2^). Participants will be defined as normal weight, overweight, or obese if their BMI index is between 18.5 and 25 kg/m^2^, greater than 25 kg/m^2^, or greater than 30 kg/m^2^, respectively, according to the age- and sex-specific cutoff standard for 2- to 18-year-old children proposed by the International Obesity Task Force (IOTF) [24, 25]. Children with overweight or obesity and some participants with normal weight (matched for sex and age with children with obesity and overweight) will be recruited to analyze their body composition, including height, weight, fat-free mass, body fat mass, body fat rate, body water, muscle mass, basal metabolic rate, total energy consumption, protein, inorganic salt, and impedance.

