#### Sexual development assessment

The primary outcome is the difference in incidence of precocious puberty between normal-weight and obese children.

Secondary sexual characteristics assessment for boys and girls will be conducted by male and female professional pediatric endocrinologists or pediatric care physicians separately in different rooms to protect the children’s privacy. Breast development will be evaluated by visual inspection and palpation. Girls with overweight or obesity will be subjected to breast ultrasound to evaluate their nodules. In boys, testicular volume (TV) will be determined by palpation and an orchidometer. According to Marshall and Tanner [26, 27], breast and pubic hair development are divided into 5 stages (stages I to V). Precocious puberty will be diagnosed according to the Tanner stage: onset of breast development stage II (B_2_) or pubic hair development stage II (PH_2_) or above before 8 years or menarche before 10 years of age in girls, and PH_2_ or testicular enlargement (TV ≥ 4 ml) before 9 years of age in boys [28–30].

The presence of early puberty will be defined as children reaching a certain stage of puberty earlier than the median age of that stage [31]. According to previous studies, the median age of puberty onset (girls: breast or pubic hair development; boys: pubic hair or testicular volume development) of Chinese adolescents will be referenced [32, 33], and the onset of menarche before 12 years of age in girls and of voice breaking before 13 years of age in boys will also be defined as early puberty [34].

We separately evaluated the tanner stage for each breast among obese girls by using portable ultrasound (US), and chose the larger one as evaluation result. Tanner II by US is characterized as the presence of a hyperechoic retro-areolar nodule with a central star-shaped or linear hypoechoic area, this stage is assumed to mark the start of breast development [35].

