#### Biospecimen collection and laboratory examination

Children with overweight or obesity and some of the participants with normal weight (matched for sex and age) will be recruited to collect venous blood at baseline; urine samples will be collected at baseline and 1-year follow-up. A total of 2 ml and 1 ml venous blood will be collected in coagulation and anticoagulation collection tubes, respectively. These participants will receive a vacuum stool collection tube and 15-ml urine tube 1 day before physical inspection, and they will be asked to collect stool and urine samples in the morning and take them to the researchers at school on the physical inspection day. All of the biological sample will be transferred with an ice bag to a local collaborating hospital within 2 hours after collection. Blood samples in coagulation collection tubes will be centrifuged to extract serum. Then, all biospecimens will be transferred with dry ice to the Biobank of Shanghai Children’s Medical Center and stored at − 80 °C.

Part of the serum sample will be used to test follicle-stimulating hormone (FSH), luteinizing hormone (LH), and estrogens (E2) in girls and testosterone (T) in boys; the residual serum will be used to test leptin, kisspeptin, and ghrelin levels. A whole-blood sample will be used to analyze the pleiotropic genes of precocious puberty and obesity.

Simultaneous quantification of 64 steroids, including EED in pediatric plasma and urine by LC–MS/MS. Using the SNaPshot technology of ultra-high throughput SNP typing to detect genetic markers, thousands of SNP loci can be detected in each reaction. ABI3730XL sequencer was used for simultaneous detection of several samples.

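### Recent hormone treatment excludes only overweight or obese children, so the groups being compared are selected by different rules; the resulting bias could go either way and its size is unknown

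*Protocol article*

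**What the plan says.** Under Study design and sampling, the inclusion rule covers every weight group: "Grade 1, 2, and 3 children (6 to 10 years old) from primary schools will be included in this study". The next sentence gives the only exclusion in the text shown. It removes "participants with overweight or obesity with a history of hormone treatment in the past 6 months as reported by parents in the questionnaire". No rationale is given and the term hormone treatment is not defined.

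The characteristic that triggers the exclusion is also the exposure. Under Physical examination: "Overweight and obesity are the main predictors of interest and will be defined by BMI value". Under Sexual development assessment: "The primary outcome is the difference in incidence of precocious puberty between normal-weight and obese children". The nested case-control study uses the same weight split crossed with pubertal status: "children with normal weight and normal puberty, with normal weight and precocious puberty, with overweight/obesity and normal puberty, and with overweight/obesity and precocious puberty". Under Biospecimen collection and laboratory examination, sex and gonadotropic hormones are measured in sampled children of both weight groups.

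Table 1 assigns the family questionnaire to all participants at every visit. The summary of its contents does not mention a medication or hormone item. The Data analysis section provides for regression adjustment for confounders without listing them.

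**The concern.** In a cohort that compares exposure groups, a restriction should apply to all groups alike unless there is a stated reason otherwise. Here a recently treated child is removed if overweight or obese and kept if normal weight or thin. Hormone treatment is not neutral for this outcome. It may alter pubertal signs, and it may be given because of a growth or pubertal problem. Treated children, with whatever pubertal status accompanies their treatment, can therefore count in the reference group but not in the exposed group.

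Three results are exposed to this:

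- the primary difference in incidence between normal-weight and obese children;
- the four nested groups, where treated children can appear only in the two normal-weight groups, and the serum hormone analyses based on them (objective III), where treatment could act directly on the measured values;
- the incidence in the general population (objective I), because the denominator lacks treated children from one weight stratum only.

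**Working it through.** **Reading the text.** The sections on design, Table 1, physical examination, pubertal assessment, biospecimens, questionnaire and data analysis were checked for a matching rule in normal-weight or thin children. None has one. The rule as written gives:

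| Weight group | Recently treated | Not recently treated |
|---|---|---|
| Normal weight (reference) | kept | kept |
| Overweight or obese (exposed) | excluded | kept |

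The protocol gives no figure for this point, so there is nothing to reproduce. What follows is illustration only.

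**Inputs.**

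- From Sample size: 4.85% precocious puberty in normal-weight and 8.43% in overweight children. The planned difference is 8.43 - 4.85 = 3.58 points.
- Assumed, with no source in the documents: h, the share of normal-weight children recently treated, 0.5% to 2%; and r, the share of those who meet the precocity definition, 0% to 30%.
- The 4.85% is taken as the risk in untreated children, which the protocol does not say.

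**Formula.** Reference risk = (1 - h) × 4.85% + h × r. The shift is h × (r - 4.85%). The exposed risk stays at 8.43% because its treated children are excluded.

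| h | r | Reference risk | Shift (points) | Difference (points) | Change in difference |
|---|---|---|---|---|---|
| 0.5% | 0% | 0.995 × 4.85% = 4.83% | -0.02 | 3.60 | +0.7% |
| 2% | 0% | 0.98 × 4.85% = 4.75% | -0.10 | 3.68 | +2.7% |
| 0.5% | 30% | 0.995 × 4.85% + 0.005 × 30% = 4.98% | +0.13 | 3.45 | -3.5% |
| 2% | 30% | 0.98 × 4.85% + 0.02 × 30% = 5.35% | +0.50 | 3.08 | -14.1% |

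The shift is zero when r = 4.85% and changes sign there. If treated children show pubertal signs more often than others, the difference shrinks. If less often, it grows.

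**Would adjustment deal with it?** Not by comparing like with like. No recently treated child remains in the exposed group, so treated normal-weight children have no counterpart. A treatment term in the regression could at most set those children aside, which is the common restriction by another route, and it needs the same data. Balancing the nested groups on sex and age does not touch the issue.

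**The case against.** The strongest reply is that the rule may be a restriction on the exposure: it may aim to remove weight gain caused by treatment, which has no direct counterpart in normal-weight children. That is plausible, but the text gives no such reason. Even then, treated children would remain in the reference group while treatment may also bear on the outcome.

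A second reply is that a symmetric exclusion has its own selection problem. If treatment is sometimes given because of precocious puberty, excluding all treated children removes true cases and lowers incidence, against the aim of describing the general population. This point stands. It is the reason for reporting incidence with and without treated children and for adding a sensitivity analysis. It does not justify excluding them from one group only.

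Third, the article is condensed and the flow chart (Fig. 1) is not shown. The confounder list may sit in the full protocol, so a reader should not infer that hormone treatment is left unadjusted. The concern does not need that inference, because it rests on an eligibility rule that is stated.

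Fourth, the numbers are soft. Both h and r are assumed, and 30% is about six times the reference rate. The 4.85% is a prevalence from previous studies that may already include treated children, in which case adding them again counts them twice. All of this stands and limits what can be said about size.

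**Conclusion.** The asymmetry is real as the article is written: one eligibility rule applies to the exposed group and not to the reference group, on a factor plausibly related to the outcome. It can bias the weight-group difference in either direction. With the assumed 0.5% to 2% treated and 0% to 30% precocious among them, the reference risk moves by about -0.1 to +0.5 points against a planned 3.58. The true effect may be negligible.

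Two stronger readings are not supported. A reader might infer that the rule definitely biases the primary result toward no difference, by some 4% to 14%. That follows only if r is fixed at 30%. With hormone treatment undefined and no count of treated children, neither the sign nor a material size can be established. A reader might also infer that treatment is on record for every child. The questionnaire goes to all participants and is named as the source for the exclusion, so this is likely, but the summary of its contents lists no such item.

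The change is worth making because it is cheap and removes the question. The finding does not invalidate the study.

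**What to change.** 1. **Eligibility text.** State one hormone-treatment criterion, the same in every weight group, for the between-group comparisons, and define the treatments it covers. The Dalian baseline was scheduled for December 2022, after the April 2022 status date, so the rule could be set there before enrolment. If the sponsor prefers the one-sided rule, its reason should be stated.
2. **Analysis filter.** In Zhongshan and Qufu, where baseline and first-year follow-up are finished, apply the same criterion at analysis to the primary comparison, the nested groups and the hormone analyses, provided the parent-reported item was recorded for all children. If it was not, say so as a limitation.
3. **Sensitivity analysis.** Repeat the comparisons keeping treated children of all weight groups wherever their data exist.
4. **General-population incidence.** Report it with and without treated children, with the number treated in each weight group.

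**Cost.** A revised eligibility sentence, one filter and one additional analysis. Table 3 shows 5395 normal-weight children in the two cities. At the assumed 0.5% to 2%, between 0.005 × 5395 = 27 and 0.02 × 5395 = 108 of them would leave the main comparison. Some may be children already sampled and matched for the nested study, so the balance of those groups on sex and age should be checked again afterwards.

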#### Sample size

Based on the formula for calculating the sample size of a cohort study at one-side significance level: [22].$$N={\left[\frac{u_{\alpha}\sqrt{2\overline{p}\left(1-\overline{p}\right)+}{u}_{\beta}\sqrt{p_1\left(1-{p}_1\right)+{p}_2\left(1-{p}_2\right)}}{p_1-{p}_2}\right]}^2$$

According to the previous studies, the prevalence of precocious puberty was 4.85% (*P*_2_) and 8.43% (*P*_1_) of children aged 7–10 years with normal weight and overweight, respectively [12, 23]. A type I error (*α*) of 0.05, u_0.05_ = 1.96;, β = 0.10, u_0.10_ = 1.28; and a loss of follow up rate of 15%, a total of 4152 children will be required in each center. Finally, inverse-variance weighting (IVW) methods will be used to adjust the sample size.

Based on the SNP gene differences between different groups reported in the literature, Quanto 1.2.4 software (John Morrison, W. James Gauderman 2009, University of Southern California) was used to estimate sample sizes for each group. According to the previous pre-experimental results of obesity study showed that the allele frequency was 0.30 and the minimum allele frequency (MAF) was 0.10 using Additive Genetic Model (ADD), the type I error (α) of 0.05, the actual Power is 0.80, we need average of 800 participants per group and 3200 cases for four groups. Cases among four groups will be controlled by sex and age.

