**Laboratory examination (participants selected for case-control study)**			
Endogenous hormones	√	√	√
Genes	√		
EEDs	√		
Gut microbiota	√		

*EEDs* Environment endocrine disruptors

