### Data analysis

Categorical variables will be reported as the number and percentage and analyzed by a chi-square test to compare the distribution between groups. The *t*-test, analysis of variance, and Wilcoxon rank-sum test will be used to compare the differences in distribution of continuous variables, which will be described by mean ± standard deviation (*SD*) for normal data or median with interquartile range for non-normal data.

Based on the discovered pleiotropic genes and obesity-related risk loci (SNPS), we will examine the distribution of gene polymorphisms (SNPS). For obesity-related SNPs of these genes, Effect size Weighting was carried out according to the method reported by Speliotes EK et al. [40], and then genetic risk scores (GRS) will been calculated using the method established in our previous study [41].That is, the number of effective Allele genes (Allele) was calculated, then the weighted value was multiplied, and finally the combined GRS of SNPs of all candidate genes in this study was accumulated.

The effects of exposure factors on outcomes will be evaluated after adjusting confounding factors using logistic regression or multiple linear regression. To analyze whether there is a linear trend of GRS among four groups: children with normal weight and normal puberty, with normal weight and precocious puberty, with overweight/obesity and normal puberty, and with overweight/obesity and precocious puberty, the Cochran–Mantel–Haenszel Trend Test will be used. After 3 years’ follow-up, a causal relationship model between exposure factors and outcomes will be established by using Mendelian randomization (MR) and Egger’s regression models and assessed by sensitivity analysis. Statistical analyses will be performed by using IBM SPSS, STATA and R statistical packages. and the level of significance will be set at *p* < 0.05.

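### Two different rules select the only genotyped children; under the weight-by-puberty rule, the obesity–precocity odds ratio in that subset reflects the sampling fractions, and unweighted Mendelian randomization there is biased

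*Protocol article*

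**What the plan says.** **Selection, first description.** Under Study design and sampling, the nested study is built from weight status crossed with puberty status: "Participants in case-control study will be enrolled in four groups: children with normal weight and normal puberty, with normal weight and precocious puberty", plus the same two puberty groups among overweight or obese children. These are the children who give blood, stool and urine and have body composition measured. The Sample size section says "we need average of 800 participants per group and 3200 cases for four groups" and adds "Cases among four groups will be controlled by sex and age".

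**Selection, second description.** The Biospecimen section says "Children with overweight or obesity and some of the participants with normal weight (matched for sex and age) will be recruited to collect venous blood". The Physical examination section recruits for body composition in the same way. Neither mentions puberty status.

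**Who is genotyped.** Table 1 lists genes, at baseline only, under "Laboratory examination (participants selected for case-control study". Anthropometry and sexual development are recorded for all participants at every visit.

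**Analyses.** The Data analysis section plans adjusted logistic or linear regression and a trend test of the genetic risk score (GRS) over the four groups. After three years of follow-up, "a causal relationship model between exposure factors and outcomes will be established by using Mendelian randomization (MR" and Egger regression. The Discussion adds the mediating role of obesity between genes and precocity. The text does not say which sample each model uses or how the sampling enters. The one mention of inverse-variance weighting concerns the sample size.

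**The concern.** Every analysis that needs a child's genotype in this study must use the nested sample. If that sample is drawn on exposure (weight) and outcome (precocious puberty) together, the exposure–outcome association inside it is decided by the sampling and no longer estimates the population association.

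An ordinary case-control study samples on the outcome alone and keeps the odds ratio. Joint sampling does not. Mendelian randomization (MR) inherits the problem, because the association of a variant with precocity that runs through weight is carried by the distorted weight–precocity link. Taking variant–obesity effects from an outside source would not repair this, since the variant–precocity association still comes from the same subset.

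At stake are the MR and mediation aims and any obesity coefficient fitted among genotyped children.

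**Working it through.** **Inputs from the protocol**
- Precocious puberty: 4.85% (normal weight) and 8.43% (overweight), Sample size section.
- Nested sample: average 800 per group, 3200 in all. As arithmetic, 4 × 800 = 3200 holds. The 800 itself cannot be reproduced, because no genetic effect size is stated.
- Two-city baseline (Table 3): 1879 overweight or obese and 5395 normal-weight children among 8623.
- Planned cohort: 4152 per center, so 3 × 4152 = 12,456.

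**Step 1. Odds ratio (OR) in the source population**
The odds are 0.0843 ÷ 0.9157 = 0.0921 for overweight and 0.0485 ÷ 0.9515 = 0.0510 for normal weight. OR = 0.0921 ÷ 0.0510 = 1.81.

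**Step 2. Four equal groups**
The cross-product is 800 × 800 divided by 800 × 800, so OR = 1.00, whatever the truth. The standard error of the log OR is √(4 ÷ 800) = 0.071, so the nominal 95% interval is 0.87 to 1.15, which excludes 1.81.

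**Step 3. Can equal groups be filled?**
- Two cities: 1879 × 0.0843 ≈ 158 overweight precocious; 5395 × 0.0485 ≈ 262 normal-weight precocious.
- Scaled by 12,456 ÷ 8623: about 229 and 378.
- Needed for 800 per cell: 800 ÷ 0.0843 ≈ 9490 overweight and 800 ÷ 0.0485 ≈ 16,495 normal-weight children.

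At these rates equal groups cannot be reached. Suppose instead that all expected precocious children are taken, with the same number c of controls from each weight group. Then OR = (229 × c) ÷ (378 × c) ≈ 0.61, on the other side of 1. This assumes that the Table 3 weight shares hold in all three cities and that no cases are added during follow-up.

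**Step 4. Selection on weight only**
With 1600 children per weight group, expected cases are 1600 × 0.0843 = 134.9 and 1600 × 0.0485 = 77.6. The odds are 134.9 ÷ 1465.1 = 0.0921 for overweight and 77.6 ÷ 1522.4 = 0.0510 for normal weight, so OR = 1.81, unchanged. The choice between the two descriptions therefore decides whether the distortion exists.

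**Step 5. Consequence for MR**
If a gene acts on puberty only through weight category, its distribution given weight and puberty depends on weight alone. With equal cells, half the precocious and half the non-precocious children are overweight, so the gene distribution is the same in both and the MR numerator is zero.

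Simulations agree. Their gene effects are assumptions, not figures from the protocol.

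GRS–precocity log-odds, with 3 million children, a GRS odds ratio of 1.5 per SD for overweight, and an effect only through weight category:

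| Sample | Log-odds |
|---|---|
| Cohort | 0.048 |
| Four equal cells | −0.004 and 0.002 (two runs; zero within simulation error) |
| All cases, equal controls per weight group | −0.051 |
| Equal cells, inverse-fraction weights | 0.046 and 0.052 (same two runs) |

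Wald ratio, with 0.4 log-odds per SD of GRS on overweight and 40,000 per cell:

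| Mechanism | Cohort | Equal cells, unweighted |
|---|---|---|
| Only through weight category | 0.141 | −0.008 |
| BMI also acts within category | 0.144 | 0.050 |
| Direct gene effect of 0.10 per SD | 0.375 | 0.265 |

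In the first row, weighting returns 0.113 and an obesity OR of 1.80. The gap between 0.113 and 0.141 is simulation error.

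**What survives.** In the direct-effect scenario, the gene coefficient adjusted for weight group was 0.099 in the cohort and 0.107 in equal cells.

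**The case against.** 1. **The groups need not be equal.** The protocol says an average of 800, and Step 3 shows that its rates cannot fill equal cells. A reader might infer that the design forces the odds ratio to exactly 1.00. The text does not support that. What stands is that the sampling fractions set the value: 1.00 and 0.61 are two alternative illustrations, and the second rests on an assumed control allocation.

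2. **Selection may be on weight only.** Blood is taken at baseline, so children whose precocity appears later cannot have been chosen for blood on that outcome. The four groups could be a later classification of a weight-selected sample. This is plausible and fits the Biospecimen and Physical examination sections. It does not fit the statement under Study design that children are enrolled in the four groups. The conflict is real and the document does not settle it.

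3. **Weights may be in the analysis plan.** The article is condensed, and its silence on weights is not itself a fault. The point rests on what is written: a jointly selected sample, a contradictory second rule, and named causal analyses that have to use that sample.

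4. **The main question is untouched.** This is correct for the primary outcome, which compares incidence between weight groups, needs no genotype, and can use the whole cohort. The GRS trend test compares scores across the four groups and does not estimate the obesity odds ratio.

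5. **Only the worst case gives a null.** The protocol's hypothesis is pleiotropy, and with direct gene effects the MR ratio is attenuated (0.375 to 0.265). This stands, and it limits the null or reversed result to genes acting only through weight category.

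**Conclusion.** The concern holds in a bounded form. The sections give two incompatible selection rules for the only genotyped children. Under the weight-by-puberty rule, the obesity–precocity odds ratio in that subset is a product of the sampling: 1.81 in the source population, 1.00 with equal groups, about 0.61 if all expected cases are taken with equal controls per weight group. Unweighted MR, mediation and obesity regressions there would be biased. The bias runs to null or reversal if genes act only through weight category, and is attenuation if BMI also acts within category or genes act directly.

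A reader might go further and conclude that the study's effect of interest is erased. The documents do not support this: the primary comparison is available in the full cohort, gene effects adjusted for weight group are largely preserved, and selection on weight alone would leave the odds ratio at 1.81.

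The odds ratios rest on the protocol's rates and Table 3. The MR figures rest on assumed gene effects and show direction and rough size only.

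**What to change.** **Selection rule.** State one rule, worded alike under Study design and sampling, Physical examination, and Biospecimen collection. Say whether puberty status is used to select children and at which visit it is determined.

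**If selection depends on puberty status.** Analyse the genotyped children as a two-phase sample. Weight each child by the inverse of the sampled fraction of its weight × puberty cell in the cohort (also by sex, age and city where these are used for selection), allow for non-participation in blood sampling, and use robust standard errors. Apply this to the variant–obesity and variant–precocity associations that feed MR, to mediation, and to any obesity model in the subset.

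**In either case.** Take the obesity–precocity effect itself from the full cohort.

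**Cost.** Wording and analysis work only. Cell sizes are available because weight and sexual development are assessed in every participant, and MR is planned only after three years of follow-up. The price is somewhat wider intervals and an assumption that, within a cell, children who give blood resemble those who do not.
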